### Participants and recruitment

2.3

The recruitment posters will be displayed in the hospitals and forward recruitment information will be posted on WeChat to recruit the potential participants for this study. The participants will be explained in detail about the potential benefits and services to be provided and the risks associated with participating in the study, including adverse clinical outcomes that may be associated with abdominal massage therapy. A detailed reading and an informed consent will be signed by each participant prior to the participation. On the consent form, participants will also be asked whether they provide consent to use their data even if they opt out of the trial. The participants will also be required to obtain permission for the research team to share relevant information with staff from the participating hospitals or regulatory agencies. The participants will receive 4 different courses of abdominal massage therapy. In addition, 30 healthy age- and sex-matched, volunteers with good sleep pattern will be recruited as the healthy controls. The personal information of all the participants will be kept confidential by the researchers and used only for this study.

The patients must properly understand and sign informed consent. Pittsburgh Sleep Index scale (PSQI), Hyperarousal scale (HAS), Hamilton Depression Scale (HAMD), and HAMA scores will be used to potentially determine whether participants meet the inclusion criteria. Patients who met the criteria will thereafter be included in the study (Fig. 1).

**Figure 1 F1:**
[figure not shown]
Trial flow chart.

### Ethical issues

2.4

This research project has been reviewed and approved by Ethics Committee of Affiliated Hospital of Changchun University of Traditional Chinese Medicine (CCZYFYLL2021 Standard word -016). This research project was funded by the National Natural Science Foundation of China (project approval Number: 82074569).

### Diagnostic criteria

2.5

#### Diagnosis of insomnia: refer to “The guidelines for the diagnosis and treatment of insomnia in Chinese Adults” (2017 edition)

2.5.1

The patient will have to display one of the following symptoms of insomnia without obvious inducement, namely decline in the sleep quality, difficulty falling asleep, persistent disorder, early awakening, or going back to sleep after waking up without completely recovering. Those patients who still have the above symptoms when they meet the sleeping conditions in a suitable environment will be considered. The major complaint will be at least one of the following sleep-related functional impairments. Fatigue or general discomfort; impaired concentration, maintenance of attention, or memory; decrease in ability to study, work and/or socialize; emotional irritability or irritability; day dreaming; behavioral problems (e.g., hyperactivity, impulsivity, interest, loss of energy; prone to errors and accidents during work or driving; tension, headache, dizziness, or other symptoms related to lack of sleep and excessive attention to sleep or dissatisfaction with the quality of sleep).

#### Diagnosis of insomnia caused by deficiency of heart and spleen: refers to TCM clinical practice guidelines for insomnia (WHO/WPO); and diagnostic criteria for insomnia of “Deficiency of heart and Spleen syndrome” in guiding principles of clinical research on new Chinese medicine (Trial)

2.5.2

The main symptoms that will be noted will be: excessive dreams, patients could easily wake and thereafter experienced difficulties to fall asleep again, palpitations forgetfulness. The major syndromes which will be noted include that of tired appearance, weak limbs unhealthy complexion, dizziness, poor appetite, thin tongue moss, and a weak pulse.

### Inclusion criteria

2.6

#### Inclusion criteria for chronic insomnia (heart and spleen deficiency type)

2.6.1

The participants will have to meet the diagnostic criteria of chronic insomnia and the TCM symptoms of heart and spleen deficiency, and fulfill the following conditions: they will have to meet the diagnostic criteria for chronic insomnia, and meet the heart and spleen deficiency related symptoms of TCM. They must be between 50 and 55 years of age. They must not have been enrolled in any other clinical studies. They will have to sign informed consent and voluntarily participate in this research. Their Pittsburgh Sleep Index (PSQI) index score must be >7, the points of the Athens (AIS) scale score must be >6. The standard score of Depression Scale (SDS) and Anxiety Scale (SAS) must be ≤60. They must not experience work and life pressure during the observation period. They must not suffer from major cardiovascular and cerebrovascular diseases and other chronic diseases; their blood and urine analysis must be normal, as well as electrocardiogram, electroencephalogram, liver and kidney function test, blood sugar, and blood lipids and other inspection indicators must fall in the normal range. Patients with the above conditions lasting >1 year and frequency ≥3 times/wk will be included in this study.

#### Inclusion criteria for healthy volunteers

2.6.2

Age 50–55, has been living in Changchun area, right-handed, moderate body size. They must have no religious belief, no tobacco, alcohol, coffee, tea, and other bad habits. They must be married with a moderate income. They must not be suffering from excessive pressure in work and life during the observation period. They must be in good health, and must not suffer from cerebrovascular disease and other chronic diseases. The woman must not be pregnant, menstruating, or lactating. The routine physical and chemical examinations such as ECG, hematuria routine, liver and kidney function, and other indicators must be normal. They must not display symptoms of insomnia, with PSQI, SAS, and SDS scores will have to be assessed as normal.

### Exclusion criteria

2.7

However, if the subject meets any of the below indicated criteria, they will not be able to participate in this trial.

Age is not in the range of 50–55 years. PSQI index is ≤7. The AIS index must be ≤6. Insomnia is being caused by excessive anxiety, depression, etc, SDS is >60 points or SAS is >60 points. They may be suffering from breathing-related sleep disorders, circadian rhythm sleep disorders, and sleep dysfunction. Patients suffering from insomnia caused by pain, fever, cough, and other diseases. Patients with severe primary diseases with internal organs and hematopoietic system. Patients with mental illness. Patients with skin infections or skin allergies at the treatment site. Progressive malignant tumors or other serious wasting diseases. Those who may have poor compliance and will not be able to treat as prescribed. Those who may be unable to judge the efficacy or incomplete data. Patients with insomnia caused by drug abuse or drug treatment. Insomnia caused by long-term excessive drinking, coffee, strong tea, and other unhealthy lifestyle related factors.

### Termination of the standard

2.8

After enrollment, the trial will be effectively terminated if one of the following symptoms occurs.

The patients suffer from the severe adverse reactions that may occur during the course of the study (medical certificate issued by the observing doctor); severe complications or deterioration of the subjects during the study period; the subjects request to willingly withdraw from the clinical study halfway; patients who may be uncooperative and have poor compliance. Additionally, if the conditions for the termination of the test must be met after being processed by the competent doctor in accordance with the standardized working procedure (SOP), the test shall be terminated immediately. The researchers will keep a detailed record of the reasons and time of withdrawal of the participants from the study. Patients who exceed at least 1/2 course of treatment will be able to enter the efficacy statistics and must properly maintain a random medical record number.

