**Methods and design::**

A single blind randomized controlled trial will be conducted. Sixty chronic insomnia volunteers and 30 healthy volunteers will be recruited for this study. Sixty insomnia volunteers will be randomly divided into a drug group and a massage group, and 30 healthy volunteers will be assigned to the healthy group. The manipulation of the treatment group will be mainly carried out through abdominal rubbing and vibration massage, once a day, 30 min/time, 5 days for a course of treatment, and a total of 4 intervention courses will be carried out. Patients in the drug group will be given orally spleen-invigorating bolus, twice a day, 1 pill in the morning and 1 pill in the evening. The course of treatment will be carried for 5 days, and a total of 4 courses of treatment will be administered.

The massage group will be compared with the healthy group and the drug group by Pittsburgh Sleep Index scale (PSQI), Hyperarousal scale (HAS), Hamilton Depression scale (HAMD), Fatigue scale-14 (FS-14), and Wechsler Adult Memory scale (WAIS) scales using to observe the sleep quality. Rs-fMRI will be used to observe various BOLD signals in the brain and compare the values of Reho, fALFF, and FC. MRS technology will be used to observe the contents of GABA and 5-HT in the hypothalamus. Additionally, the contents of cortical hormone releasing hormone (CRH), adrenocorticotropic hormone (ACTH), COR, GABA, NE, PGE2, and 5-HT in the serum will be also detected. The serum of each group will be taken for 1H nuclear magnetic resonance (^1^HNMR) metabolomics study to analyze the various common metabolites, differential metabolites, potential metabolic biomarkers, and metabolic pathways among the 3 groups. Finally, in combination with the brain functional imaging and brain spectrum, the potential mechanism of abdominal vibration and ring massage will be discussed.

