### Setting

2.2

The patients will be recruited from the Department of Zang-fu Massage, Affiliated Hospital of Changchun University of Chinese Medicine. Additionally, for participating in the trial, the patients will be screened strictly according to the diagnostic criteria, inclusion criteria, and exclusion criteria, and the requirements for the sample size estimation will be based on the clinical calculation formula employed for small sample size. The sample size (n = 16.76) will be calculated, that is, the therapeutic effect could be judged by the sample size of >16.67 people in each group. In this study, therefore 30 people will be observed in each group, which met the sample size estimation criteria.

The trial researcher will be able to record the subject's basic information (such as date of birth, sex) and answer patient trial screening questions. After the various patients have completed screening and enrolled, the trial study serial number, that is, the patient's unique identification number (SIN), will be obtained according to the enrollment time and order of enrollment, until the total number of observations (30 cases) was completed. Thirty healthy volunteers and 30 patients will be recruited for the study. After clinical evaluation and blood sampling, abdominal massage therapy will be adopted.

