### Stripping and shedding criteria

2.9

After enrollment, patients who meet one of the following criteria will be terminated from the trial.

Exclusion criteria: Those who might fail to meet the inclusion criteria and have entered the study; those who might to follow the prescribed treatment or incomplete data affecting the efficacy evaluation and safety evaluation; those who might have used the different therapeutic methods prohibited by this protocol; and those who might change the treatment plan midway by themselves.

Shedding criteria: The subjects with poor compliance and self-withdrawal during the course of treatment; those who might display serious adverse events or in those in which complications might occur; and those who will be unable to continue the treatment for various reasons.

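### Sections 2.8 and 2.9 tie entry to the efficacy analysis to behaviour after randomisation, use an undefined half-course threshold, and leave unclear whose data are analysed

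*Protocol article*

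**What the plan says.** The Abstract (Methods and design) sets up the randomised comparison: "Sixty insomnia volunteers will be randomly divided into a drug group and a massage group". Section 2.2 plans 30 per group.

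Section 2.8 terminates participation after enrolment for severe adverse reactions, complications or deterioration, a request to withdraw, or poor compliance. It then gives the entry rule: "Patients who exceed at least 1/2 course of treatment will be able to enter the efficacy statistics".

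Section 2.9 gives two further lists of enrolled patients who are terminated from the trial.
- The exclusion (stripping) list covers patients who turn out not to meet the inclusion criteria, patients who use prohibited treatment or change treatment themselves, and "those who might to follow the prescribed treatment or incomplete data affecting the efficacy evaluation and safety evaluation". The last item is garbled and presumably means failing to follow treatment.
- The shedding list includes "The subjects with poor compliance and self-withdrawal during the course of treatment; those who might display serious adverse events", and those unable to continue for other reasons.

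Neither list mentions a half-course exception.

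Two eligibility items refer to things not fully known at entry. Section 2.7 lists "Those who may be unable to judge the efficacy or incomplete data". Section 2.6.1 requires of patients: "They must not experience work and life pressure during the observation period".

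Section 2.3 asks participants whether their data may be used even if they leave the trial.

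**The concern.** Randomisation makes the two patient arms comparable as allocated. Once inclusion in the analysis depends on adherence, tolerance, withdrawal or completeness of data, the arms compared are partly chosen by the patients' response to treatment.

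The arms differ in burden: a 30-minute hands-on session once a day against one pill morning and evening. Equal dropout for equal reasons cannot be taken for granted. The comparison at risk is the only randomised one in the study, since the healthy group is not randomised.

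Two analysts following the text could also build different datasets, because sections 2.8 and 2.9 cover overlapping patients in different terms and the half-course threshold has at least two meanings.

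**Working it through.** **1. The two sections side by side**

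| Reason after enrolment | Section 2.8 | Section 2.9 |
|---|---|---|
| Withdrawal | Terminated; may enter efficacy statistics past half a course | Shed; no exception stated |
| Poor compliance | Same | Shed; no exception stated |
| Severe or serious adverse event, complication | Same | Shed; no exception stated |
| Not following treatment, self-changed or prohibited treatment | Not listed separately | Stripped; no exception stated |
| Incomplete data | Not listed | Stripped; no exception stated |

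A patient who withdraws in the third course falls under both sections. Section 2.8 admits that patient to the efficacy statistics; section 2.9 does not say either way.

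**2. The threshold**

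Inputs (Abstract and section 2.10): 5 treatment days per course, 4 courses. Total = 4 × 5 = 20 treatment days.
- Half of one course: 5 / 2 = 2.5, so the first whole day past it is day 3. 3 / 20 = 15%.
- Half of the programme: 20 / 2 = 10. 10 / 20 = 50%, or 11 / 20 = 55% if the threshold must be strictly exceeded.

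**3. Is power the problem?**

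The article's only related figure is the required size per group, printed in section 2.2 as 16.76 and as 16.67. It cannot be reproduced, because no effect size, SD, power or sidedness is given. Assuming a two-sided 5% test and 80% power, 16.76 implies an effect of √(2/16.76) × (1.960 + 0.842) = 0.97 SD. At that effect, power is 96% with 30 per arm and 81% with 17. On these assumptions, loss of numbers is not the main issue.

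**4. Size of the bias (illustration)**

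Let a fraction f of an arm be removed, with outcomes s SD worse than those kept. The full-arm mean is the kept mean minus f × s, so the kept patients overstate the arm by f × s. With removal in both arms, the bias in the difference is f₁s₁ − f₂s₂. The values of f and s are assumptions.

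| Removed from one arm only | s | Bias |
|---|---|---|
| 10% (3 of 30) | 0.5 SD | 0.05 SD |
| 20% (6 of 30) | 1.0 SD | 0.20 SD |
| 30% (9 of 30) | 1.5 SD | 0.45 SD |

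If both arms lose 20% with s = 1, the bias is 0.20 − 0.20 = 0. If one loses 20% and the other 10%, both with s = 1, it is 0.20 − 0.10 = 0.10 SD. For scale, 30 per arm can detect about 0.74 SD (two-sided 5%, 80% power, both assumed).

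**5. Effect on false positives (illustration)**

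In 20,000 simulated trials with 30 per arm and no true effect, the share q of one arm with the lowest compliance score was removed. The score correlates ρ with outcome. The theoretical bias is ρ × φ(z_q) / (1 − q), where φ is the standard normal density and z_q the normal quantile at q. For q = 20% and ρ = 0.5 it is 0.5 × 0.280 / 0.80 = 0.18 SD.

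| q | ρ = 0.3: bias, type I error | ρ = 0.5 | ρ = 0.8 |
|---|---|---|---|
| 10% | 0.06 SD, 5.6% | 0.10 SD, 6.5% | 0.16 SD, 9.8% |
| 20% | 0.11 SD, 6.4% | 0.18 SD, 10.1% | 0.28 SD, 18.5% |
| 30% | 0.15 SD, 7.5% | 0.25 SD, 13.8% | 0.40 SD, 30.3% |

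The nominal rate is 5%. Again q and ρ are assumptions, and removal is in one arm only.

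**The case against.** The strongest defence is that the two sections can be read together. Section 2.9 says who leaves the trial, and section 2.8 says which of those still enter the efficacy statistics. Section 2.9 never says that data already collected are dropped, and the consent question in section 2.3 suggests that data from patients who leave are meant to be used. A reader might infer a flat contradiction; the text supports only an ambiguity. It leans towards exclusion, because section 2.9 gives damage to the efficacy evaluation as a ground for stripping. Likewise, that only patients past half a course enter is an inference from there being a threshold, though a threshold has little purpose otherwise.

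Three further readings go too far.
- **Life stress as a reason for removal.** Neither section 2.8 nor 2.9 lists it. It arises only by joining the section 2.6.1 criterion to the section 2.9 item on patients who fail the inclusion criteria, and that item reads most naturally as enrolment in error.
- **Poor compliance in section 2.7 as a breach of randomisation.** It stands under who may participate and is a forward-looking screening judgement.
- **Adverse events going uncounted.** The half-course rule concerns efficacy only, section 2.8 requires the reasons and time of withdrawal to be recorded, and nothing says that events are left out.

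It is also fair that the bias figures assume removal in one arm only, while the rules apply to both. Analysis-set definitions and missing-data methods are often left to a fuller document. That does not dispose of the point: the article itself states who may enter the efficacy analysis, and makes this depend on treatment received.

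**Conclusion.** The concern holds in this form. Section 2.8 makes entry of terminated patients to the efficacy analysis conditional on treatment received after randomisation. Section 2.9 strips or sheds randomised patients for overlapping and further reasons without saying whether the same condition applies. Nothing in the article restores an analysis of all randomised patients. The massage-drug comparison is therefore open to selection bias, and the analysed set cannot be determined from the text.

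The threshold ambiguity, 15% against about 50% of treatment, follows directly from the article's own schedule. The size of any bias does not: it rests on assumed removal rates and prognosis, runs from 0.05 to 0.45 SD in the one-arm cases shown, and would be near zero if removal were alike in both arms. The documents do not show that bias of a given size will occur, only that the stated rules permit it.

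**What to change.** - Reconcile sections 2.8 and 2.9 by separating stopping treatment from leaving the analysis. The clinical stopping rules themselves are not touched.
- Make the primary efficacy set all randomised patients, analysed in the arm allocated.
- Use the half-course rule and the section 2.9 criteria only to define a per-protocol sensitivity set. State the threshold as a number of treatment days out of 20, and whether reaching it suffices. Treatment days fit both arms; massage sessions do not describe the drug arm.
- Continue the PSQI at the planned times after treatment stops in patients who agree. Section 2.3 already seeks consent to use data after opting out; agreement to further questionnaires should be added if it is not covered.
- As a secondary point, reword the incomplete-data item in section 2.7 and the work-and-life-pressure item in section 2.6.1 so that both are judged at entry and cannot be used through section 2.9 to remove randomised patients later.

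The cost is protocol wording, a few extra questionnaires and a possibly smaller estimated effect. No additional patients are needed.

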### Stripping and shedding criteria

2.9

After enrollment, patients who meet one of the following criteria will be terminated from the trial.

Exclusion criteria: Those who might fail to meet the inclusion criteria and have entered the study; those who might to follow the prescribed treatment or incomplete data affecting the efficacy evaluation and safety evaluation; those who might have used the different therapeutic methods prohibited by this protocol; and those who might change the treatment plan midway by themselves.

Shedding criteria: The subjects with poor compliance and self-withdrawal during the course of treatment; those who might display serious adverse events or in those in which complications might occur; and those who will be unable to continue the treatment for various reasons.

### Treatment programs

2.10

After being enrolled, 30 patients will be treated with abdominal vibration and ring kneading therapy. The main techniques that will be used include rubbing the abdomen, shaking the abdomen, and pressing the abdomen. The main points to be considered will be Zhongwan (CV12), Shenque (CV8), Zhongji (CV3). The acupoint location that will be used refers to the 2006 National Standard of the People's Republic of China (GB/T12346-2006) “Acupoint Name and Location.”

During the treatment, room temperature will be kept appropriate, and the environment quiet and tidy. The patient will be laid in the supine position, exposing the abdomen and maintain it in a relaxed state. The doctor will sit on the right side of the patient. The doctor will rub the entire abdomen clockwise with CV 8 as the center for 5 minutes, up to CV 12, and down to CV 3. The left and right sides will be placed between the left and right meridians of the foot Taiyin Spleen meridian, so as to regulate the air movement and allow the blood to flow. Thereafter, the whole abdomen will be kneaded with both hands for 10 minutes to adjust the internal organs and to balance the yin and yang. CV 12 will be vibrated with one hand for 2 minutes, palm CV 8 for 3 minutes, and flash CV 3 for 5 minutes with one hand, at a frequency of >200 times per minute to invigorate the spleen and stomach, and replenish qi and blood. Thereafter, abdomen will be pressed with the palm of the hand centered on CV 8, it will be pressed deeply while breathing in, and will be lifted gently while breathing out, for 5 minutes, to induce the air to return to the original body, and to calm the mind. Patients will undergo the therapy for 30 minutes duration each time, once a day, 5 days as a course of treatment, the treatment interval will be 2 days, and intervention will be conducted over 4 courses. There will be a follow up conducted once during the 4th week after the treatment.

